### Study measures

To address Specific Aim 1 (implementation effectiveness), we measure the following implementation outcomes: Reach, Adoption, Implementation, Maintenance, and Equity [45]. To evaluate Specific Aim 2 (patient effectiveness), we measure two patient outcomes in line with the Effectiveness element of RE-AIM: Stimulant Abstinence and Treatment Retention. Finally, in pursuit of Specific Aim 3 (exploratory mediators), we evaluate contextual determinants as putative mediators of implementation outcomes; specifically, we assess implementation strategy progress, inner setting factors, and provider characteristics. Table 1 presents a detailed overview of study measures by Specific Aim.

**Table 1 Tab1:** Description of study measures, data source, and timing of measurement

Outcome	Definition	Data source	Frequency and timing of measurement
*Aim 1*			
Reach	Calculates patients’ exposure to contingency management (CM) by dividing the number of newly admitted patients with recent stimulant use (defined as documented patient-reported stimulant use or a positive stimulant urine screen within the first 30 days of treatment) who received 1 or more CM encounters by the total number of newly admitted patients with recent stimulant use.	Electronic medical records (EMR) CM tracking tool	End of each wedge
Adoption	Calculates the proportion of providers who have adopted CM by dividing the number of counselors who delivered 1 or more CM encounters divided by the total number of counselors.	EMR CM tracking tool	End of each wedge
Implementation	Assesses delivery of CM with fidelity in two ways: 1. Proportion of counselors meeting the fidelity target on the CM Competence Scale (a mean overall score ≥ 4.0), which rates 9 CM elements on a scale from 1 (not at all present) to 7 (fully present) 2. Proportion of CM sessions covering ≥ 7 of 9 of the standard CM elements, as assessed by a self-report checklist in the CM tracking tool.	Observer rating CM tracking tool	Role play following Preparation phase End of each wedge
Maintenance	Measures Reach, Adoption, and Implementation throughout the Sustainment phase.	EMR CM tracking tool Observer rating	End of each wedge during Sustainment phase
Equity	Evaluates whether the above systematically vary based on race/ethnicity, biological sex, gender, and other sociodemographic factors of patients and providers.	EMR Provider survey	Baseline
*Aim 2*			

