### Data analysis

Across 2400 EMR pulls, 720, 480, and 1200 are expected to occur during Usual Care, Preparation/Implementation, and Sustainment phases, respectively. Preliminary analysis will include bivariate and multivariate analysis using correlations, cross-tabulations and regression models to ascertain data structure, statistical distribution, and study artefacts. Analyses for all Aims will be performed using multilevel structural equation models (MSEM) in Mplus 8.10 [51]. We conducted Monte Carlo simulation power analyses modeling treatment effects and outcome variance nested in OTPs (anticipated ICC: 15%) and/or counselors (anticipated ICC: 10%; see Table 2). There is no expected missing data from EMR pulls, although at OTP and counselor levels, analyses will follow an intent-to-treat approach to dealing with missing data. Across all analyses, we will employ a moderator-first approach to the equity of treatment effects to ensure that group-level differences can be validly interpreted and that we are sensitive to differential treatment effects among patient subgroups. Similarly, we will examine whether significant variance in treatment effects occurs at counselor- or OTP-levels (through exploring the size of random effects variance parameters) before concluding whether treatment effects can be validly interpreted as fixed at the patient-level.

**Table 2 Tab2:** Results of Monte Carlo simulation analyses examining power to detect aim 1 and aim 2 outcome effects

Outcome	Comparison (*n* per condition)	Predicted rates/effects	Power at α = .05
*Aim 1*			
Reach^a^	Usual care (720)–preparation/implementation (480)	2–22%	98%
Adoption^b^	Usual care (70)–preparation/implementation (70)	10–50%	95%
Implementation	No comparison		
Maintenance	Preparation/implementation (480)–sustainment (1200)		
*Aim 2*			
Stimulant abstinence	Usual care (720)–preparation/implementation (480)	25–40%	90%
Treatment retention	Usual care (720)–preparation/implementation (480)	9 weeks–12 weeks	94%

Monte Carlo simulation multilevel power analyses featuring clustering in opioid treatment programs (anticipated ICC: 15%) and/or counselors (anticipated ICC: 10%)

^a^Assessed among patients nested in counselors and opioid treatment programs

^b^Asssessed among counselors nested in opioid treatment programs

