Aim 1 hypotheses (effect of SSL on CM Reach and CM Adoption) will be tested by examining the effect of treatment condition at a given center at a given time point, for patients nested in counselors in centers (3-level model). Generalized linear mixed models will be used to evaluate treatment effects on rates of CM Reach, Adoption, and Maintenance.

For Aim 2 analyses, generalized MSEM models will be used to model the effect of SSL implementation. Using data from prior CM trials, we assume a rate increase for Stimulant Abstinence from 25 to 40% following SSL receipt, and a treatment retention increase of 30% from 9 to 12 weeks following SSL.

For Exploratory Aim 3 analyses, MSEM models will be used to assess whether putative provider-level mediators that will be assessed via the provider surveys (e.g., implementation climate, implementation leadership, CM perceptions) are associated with change in implementation outcomes. Exploratory outcome analyses will measure putative mediators as latent factors combining measures of SSL fidelity, inner setting factors, and provider characteristics, to assess the extent to which latent factors serve as mechanisms of action for the main effect of the SSL on implementation outcomes using bootstrapped confidence intervals.

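### The Aim 1 analysis sentence gives Adoption a patient-level three-level model, but Table 1 defines Adoption per counselor and Table 2 powers it per counselor

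*Protocol article*

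**What the plan says.** All places are in the protocol article.

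- **Data analysis, Aim 1 paragraph.** "Aim 1 hypotheses (effect of SSL on CM Reach and CM Adoption) will be tested by examining the effect of treatment condition", and the same sentence ends by saying that this is done "for patients nested in counselors in centers (3-level model". Both outcomes receive one structure. The next sentence names generalized linear mixed models for the rates of Reach, Adoption and Maintenance, but gives none of them a unit of its own.
- **Study measures, Table 1.** Adoption is obtained by "dividing the number of counselors who delivered 1 or more CM encounters divided by the total number of counselors". It is assessed when each wedge ends.
- **Data analysis, Table 2.** The Adoption row compares "Usual care (70)–preparation/implementation (70") for a rise from 10% to 50%, with 95% in the column headed "Power at α = .05". Its footnote b reads "Asssessed among counselors nested in opioid treatment programs". The Reach row carries a different footnote: "Assessed among patients nested in counselors and opioid treatment programs".

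**The concern.** Adoption is a primary-aim outcome, and the only sentence that states the structure of its model gives it a level at which it does not exist. A patient either received contingency management or did not, so Reach can be modelled on patients. Adoption is a property of the counselor.

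To fit Adoption in the stated model, an analyst would have to write each counselor's yes/no on all of that counselor's patient rows. That has three consequences:

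- Counselors count in proportion to caseload, so the estimate is no longer the Table 1 proportion.
- A counselor with no eligible patient has no row, yet still belongs in the Table 1 denominator.
- The copies can pass for independent evidence on the SSL effect. A counselor random intercept absorbs copies that never change within a counselor. It does not absorb copies of a status that is scored once under usual care and again under SSL.

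**Working it through.** **1. The passages side by side.** Table 1 (counselors over counselors), the Table 2 sample size (70 v 70 counselors) and Table 2 footnote b (two levels) all make the counselor the unit. The Aim 1 sentence makes it the patient (three levels). Its structure matches footnote a, which belongs to Reach.

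**2. Does the stated 95% power rest on counselors?** Inputs: 70 per condition, 10% v 50%, OTP ICC 0.15 (Table 2); 70 counselors in 10 OTPs (Participant recruitment), so 7 per OTP; two-sided 0.05 (assumed).

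- Design effect = 1 + (7 − 1) × 0.15 = 1.9; effective n = 70 / 1.9 = 36.8.
- Null SE = √(2 × 0.3 × 0.7 / 36.8) = 0.107; alternative SE = √((0.09 + 0.25) / 36.8) = 0.096.
- Pooled normal: Φ[(0.40 − 1.96 × 0.107) / 0.096] = 97.6%.
- Continuity-corrected: 95.6%. Noncentral t on 9 df: 95.8%. Wald on the log-odds scale: 92.9%. No clustering: 99.98%.

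The stated figure is compatible with counselors in OTPs. The simulation code behind it is not shown.

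**3. How many copies?** Data analysis expects 720 usual-care and 480 preparation/implementation pulls. Per counselor that is 720 / 70 = 10.3 and 480 / 70 = 6.9 rows.

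**4. Closed-form check of literal use.** Take a before/after layout with the same counselors in both conditions, m0 = 10 and m1 = 7 copied rows, a counselor effect in the model and no SSL effect. Let d be a counselor's change in status.

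- True variance of the estimate = Var(d) / 70.
- Residual variance seen by the model = [m0·m1 / (m0 + m1)] × Var(d) / (m0 + m1 − 1).
- Reported variance = that × (m0 + m1) / (70·m0·m1) = Var(d) / [70 × (m0 + m1 − 1)].
- Ratio of reported to true variance = 1 / (10 + 7 − 1) = 1/16, so the SE is a quarter of what it should be.
- Type I error = 2 × [1 − Φ(1.96 / 4)] = 2 × [1 − Φ(0.49)] = 62%.

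**5. Simulations with no SSL effect.** Linear models stand in for the GLMM, with 10 OTPs and ICCs of 15% and 10% on the latent scale. The first and the stepped layouts use usual-care and active intervals only. The first and third rows take 48 patients per OTP per 6 months (8 per month).

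| Layout | Patient rows | Counselor rows |
|---|---|---|
| Counselor fixed effects, period terms; 4 / 7 counselors per OTP; 600 runs | 67% / 57% | 4% / 5% |
| Before/after, random intercepts, 7 per OTP; true rate 10% / 30%; 250 runs | 64% / 58% | 3% / 6% |
| Stepped 2/2/3/3, period terms, 250 runs: 4 per OTP with 0, 16 or 32% turnover per interval; 7 per OTP with 0 or 16% | 62–70%; 54–57% | 3–8% |
| Stepped, period terms, counselor random intercept only; 4 or 7 per OTP; 100 runs | 59–74% | – |
| Same, plus counselor-level random SSL effect | 10–16% | – |
| Before/after, each counselor in one condition only; true rate 10%; 300 runs | 0.3% | 5% |

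Monte Carlo error is about √(0.6 × 0.4 / 250) = 3 points for 250 runs and √(0.13 × 0.87 / 100) = 3 points for the 10–16% row. The 0.3% comes from a near-degenerate fit whose residual variance is close to zero. It shows no inflation, but it is not a sound test either.

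**6. Records if counselors are scored per interval.** At 8 patients per month, one OTP-interval of 6 months has 48 pulls. Then 720 / 48 = 15 usual-care and 480 / 48 = 10 active OTP-intervals. With 7 counselors per OTP this is 105 v 70 counselor records; with 4 it is 60 v 40. Neither is 70 v 70.

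**The case against.** The best defence is that the Aim 1 sentence is shorthand. Three other statements point to counselors, and the power note says that nesting is in OTPs and/or counselors, so the levels were meant to vary by outcome. The article nowhere says that a counselor's value will be written on patient rows. Multilevel structural equation modelling, named for all aims, allows an outcome to sit at the counselor level. The full analysis plan, which is not shown, may do exactly that.

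Shorthand is plausible. It explains the contradiction but does not remove it: the stated model still names Adoption and still has patients at its lowest level.

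A second defence concerns size. Data analysis also plans to examine whether the treatment effect varies across counselors or OTPs before treating it as fixed at the patient level. With a counselor-level random SSL effect, type I error on copied rows falls to about 10–16%. This stands, and it limits what can be said about the plan as a whole.

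A third is turnover: the Provider turnover plan reports 32% of counselors leaving within a 6-month active phase, so overlap between conditions is only partial. With 4 counselors per OTP, turnover at that rate left the inflation in place; with 7 per OTP that rate was not run.

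A reader might infer that the planned Adoption test will give false positives more than half the time. The documents do not support that. It needs the copying step, which they do not state, the same counselors scored in both conditions, and a constant SSL effect.

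**Conclusion.** The contradiction holds. The three-level patient model fits Reach and is wrong for Adoption as Table 1 defines it and Table 2 powers it. The Table 2 power figure is consistent with counselors as the unit and is not in question on this ground.

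The damage is conditional. Literal use with copied rows would change the estimand through caseload weighting and lost counselors. Where counselors are scored in both conditions, it would also raise type I error to about 55–70% with a constant SSL effect, or about 10–16% with a counselor-level random SSL effect. Counselor-level rows give 3–8%. Overlap is likely, because 70 v 70 come from an estimated 70 counselors in total and Adoption is measured wedge by wedge, but it is not certain. With each counselor in one condition only there is no inflation.

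The rates rest on linear approximations to the GLMM, equal or Poisson caseloads, and 4 or 7 counselors per OTP. Read them as indicative.

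**What to change.** In the Aim 1 paragraph, limit the three-level patient model to Reach. Then add a sentence for Adoption, in substance: *Adoption is analysed with the counselor as the unit, nested in OTPs as in Table 2 footnote b, with a counselor random effect if counselors are scored in more than one interval.*

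If the intention is one record per counselor per interval, say so. Say also that this differs from the two-level, 70 v 70 basis of the stated 95% power, and check that figure on the same records (for example 105 v 70 or 60 v 40, depending on counselors per OTP).

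The cost is one or two sentences and, if interval records are chosen, a rerun of one power simulation. No new data are needed. Recruitment had not begun when the article was written (Trial status).

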### Trial status

No organizations or providers have been officially enrolled yet; recruitment is slated to begin in January 2024.

## Discussion

### Changes to the national landscape in between peer review of this proposal and funding

The national landscape surrounding CM has shifted dramatically from the time the project was originally proposed to when the project was funded. In the last 2 years, CM began making national headlines, including a New York Times article about the CM research-to-practice gap in Fall 2021 titled, “This addiction treatment works. Why is it so underutilized?” [52] and an Associated Press feature titled, “Candy, cash, gifts: How rewards help recovery from addiction” [53]. Moreover, after decades of advocacy, the state of California has decided to pilot CM as a Medicaid reimbursable service, an initiative that is being watched closely by other Departments of Health across the country. At the same time, states across the country have started to receive significant funding to address the overdose crisis via both the Substance Abuse and Mental Health Services Administration (SAMHSA) and the federal opioid settlement; reflecting the national enthusiasm for CM, some SAMHSA grant mechanisms have explicitly referenced a need for all grantees to receive CM training in the first year of funding. The more favorable national landscape for CM has affected the approach of many Departments of Health, engendering a strong desire to provide CM training to OTPs across the state as quickly as possible.

For this reason, when we connected with several Departments of Health to launch recruitment for this study, we were met with resistance to OTPs being randomized to a delayed training date. Specifically, Departments of Health noted that they were required to offer CM training to OTPs in their states and that they were not comfortable withholding training for an extended period. At that point, our team was faced with a critical conundrum that frequently plagues implementation scientists: how to balance rigorous research design with real-world priorities.

We ultimately made two changes to ensure the stepped-wedge trial would be acceptable to our partners. First, we substantially condensed the study timeline so that the longest an OTP would need to wait for intensive support would be 2 years. We had initially proposed a stepped wedge trial spanning 60 months (a timeline considered acceptable by our partners when we wrote the protocol, but far too slow once the protocol was funded), and we refined our timeline to 30 months. Second, we agreed to provide all OTPs participating in the study a 1-h self-paced webinar on CM immediately after the study start-up phase, to satisfy SAMHSA grant requirements and address the needs of our Department of Health partners. When we wrote the initial proposal, we presumed that OTPs would not have received any CM training; we now more realistically expect OTPs to have received basic CM education, as expected by SAMHSA and other state funders. This design will enable us to evaluate whether the full SSL strategy is superior to real-world implementation as usual, since CM webinars and brief training encounters are becoming more commonplace. In our experience working with the New England ATTC, organizations are highly unlikely to successfully implement a behavioral intervention like CM after a brief training encounter (please see our recent commentary, in which we noted the insufficiency of “one shot training” for greater discussion of this issue [15]); therefore, we do not expect the provision of this webinar to have any notable effect on our power assumptions or sample size calculations.

### Potential impact of protocol

Results of the current protocol have the potential to improve the quality of care in OTPs. Lessons learned may inform future implementation of evidence-based behavioral treatments in OTPs, a treatment setting that serves high-need, under-served patients at high risk of lethal overdose. Information gained may also inform efforts to improve CM implementation in other critical public health settings where CM has demonstrated effectiveness (e.g., HIV/AIDS care, prenatal care) [54, 55]. Given the dearth of knowledge on why and how implementation strategies work, our focus on specification and evaluation of contextual determinants will advance the scientific study of methods to integrate research findings and evidence-based interventions into healthcare practice and policy.

The impact of this study will be heightened by it being situated within a center of excellence in which all three major research components use common implementation strategy tracking tools and implementation outcomes. In addition, two Departments of Health have asked our team to partner with them to evaluate their state-wide efforts to fund CM implementation; we will strategically use the SSL strategy, the same implementation adherence tools, and the same set of implementation and patient outcomes to enable comparisons across initiatives. By carefully specifying and tracking the SSL strategy across these companion initiatives, our methods will help to unpack the “black box” of implementation strategy selection and deployment that so often plagues implementation science research.

## Data Availability

Data collected as part of this study protocol, as well as the Data Safety Monitoring Plan, can be requested from the contact Principal Investigator, [name].

## Abbreviations

CM: Contingency management
OTP: Opioid treatment program
SSL: Science to Service Laboratory
VA: Veteran’s Administration
